**15. Criteria for suspension and dropout**

**(3) Justice**

Subjects who have completed the late evaluation according to the clinical trial protocol are considered to have completed the trial. The completion of the trial of all subjects participating in the clinical trial should be recorded, and if the visit or observation was interrupted, the reason should be stated.

**(4) Criteria for stopping clinical trials**

V. If the circumstances observed during the clinical trial make it unreasonable to proceed with the clinical trial, the principal investigator must request the clinical trial to be suspended to the clinical trial review committee can be stopped.

VI. **Investigator** wishes to suspend a clinical trial for reasons such as safety of a clinical trial medical device, he/she may request to suspend the clinical trial to the clinical trial review committee and suspend the clinical trial according to the decision of the clinical trial review committee.

VII. In case of temporary suspension for the treatment of adverse events that have occurred

VIII. Suspension due to the occurrence of serious adverse events and abnormal medical device reactions

**(5) Discontinuation of clinical trials**

clinical trial stopped case The clinical trial director stopped up to the point proceeded A 11 clinical

trial related data in summary The principal investigator will keep it and discard it according to the procedure.

III. When a clinical trial is suspended, the clinical trial director must organize and deliver the case record, clinical trial progress, and results for the subjects who have progressed up to the time of the suspension to the principal investigator and return all test-related data (case records) to the principal investigator.

IV. If the clinical trial is discontinued, the clinical trial director must immediately notify the subject of the discontinuation of the trial, ensure that appropriate measures and follow-up can be made, and notify the trial review committee in writing.

#### **(4) The subject's leaving out standard**

X. If the study is discontinued at the request of the subject or his/her representative

XI. Clinical trial to the result Affect line Number there is surgery, drug or medical device in parallel used case

XII. Clinical trial properly not done not case

XIII. Subject's by absence Inability to conduct early and late evaluations case

XIV. Withdrawal of consent at the request of the subject or his/her representative

XV. In case tracking is not possible due to non-scheduled visit

XVI. In case the subject dies due to reasons not related to the clinical trial

XVII. When the investigator determines that the suspension of the test is beneficial to the subject

XVIII. If the other investigator determines that there is a problem with the clinical trial

On the other hand, if the study is stopped due to safety problems due to the occurrence of adverse events or worsening of complications, the principal investigator shall take appropriate measures and follow -up until possible symptoms are recovered. Relevant information should be recorded in the case record.

#### **(5) Investigator dropout**

IV. If a subject is dropped out, the reason for dropping out and the data related to the clinical trial conducted before the dropout shall be recorded and kept.

V. Dropouts are included in statistical processing through safety and efficacy evaluation

unless there is a justifiable reason or justification.

VI. For data obtained through clinical trials, a data set for efficacy analysis and safety analysis should be established.

When information cannot be judged due to insufficient or conflicting information and cannot be supplemented or verified

#### **(8) Evaluation criteria for safety**

by subject in the case record described Adverse events, vital sign, laboratory test result consider evaluation

#### **(9) How to evaluate safety**

**Vital signs and laboratory tests:** For each evaluation, discomfort and skin problems are evaluated at each visit, and a safety evaluation questionnaire is filled out after the test.

#### **(10) How to report adverse events**

##### **III. Adverse case**

Adverse case of anomalies summary and analysis is for clinical trials Medical Equipment apply after occurred Adverse events (TEAE) about Analyz.

Application group not really Adverse events (AE), medical devices Adverse event (ADE), serious Adverse events (SAE) Descriptive statistics for incidence and manifestation number of cases) present between application groups Adverse events (AE), medical devices Adverse event (ADE), serious Adverse event (SAE) incidence. The difference whether Pearson's chi-square test or by Fisher's exact test analyze.

Expressed every Adverse events (AE), medical devices Adverse events (ADEs) and serious Adverse events (SAE) about MedDRA latest version using System Organ Class (SOC) and Preferred Term (PT) according to to code coded Adverse case number of expression subjects, expression rate and the number of manifestations by county present. Also serious in an abnormal case about details write

##### **IV. Serious adverse events**

Serious abnormal case safety follow up term within occurring If , over case of Whether or not related to clinical trials Clinical Investigator or the test officer 24 hours to the Korea Textile Development Institute within report , and term within to the IRB have to report do \_

**17. Effect evaluation criteria, evaluation method and interpretation method (statistical analysis method, etc.)**

All X-ray readings are performed by 3 specialists in a blinded state, and all are analyzed and the average value of the overall evaluation results is used.

**(1) Data analysis and statistical analysis method**

1. Primary efficacy endpoint: hip dislocation through radiographic evaluation (%)
2. Secondary efficacy endpoints: degree of scoliosis through plain radiograph; pain index, Functional changes such as satisfaction with wearable medical devices for hip joint protection, hip and knee joint range of motion, discomfort when caring for a patient, and changes in the patient's overall quality of life were investigated.

The clinical evaluation is statistically compared between the initial and simple X-ray results after 1 year (compare with paired t-test or Wilcoxon signed rank test according to normality test). In addition, the difference in change values for the initial, 6 months, and 1 year after simple X-ray imaging and clinical evaluation is statistically compared. Repeatedly measured values are verified by a linear mixed model or a generalized estimating equation (GEE) between the experimental group and the control group. If the P-values are  $< 0.05$ , it is judged to be a significant level.

Dropout, all data including in statistical processing (ITT) will be analyzed through safety and efficacy evaluation, unless there is a valid reason or justification. When missing values occur in the FAS group, they are excluded and analyzed because it is difficult to satisfy the assumption of Missing Completely at Random (MCAR).

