## **(4) Hip dislocation test**

Hip subluxation and dislocation can be evaluated by plain X-ray (Hip AP radiography). Migration index, which measures the proportion of the femoral head not covered by the hip acetabulum, is widely used. Measured at initial, 6 months, and 12 months.

[figure not shown]

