## 1.7 Data Analysis and Statistical Analysis Methods

- The clinical evaluation is statistically compared between the initial and simple X-ray results after 1 year (compare with paired t-test or Wilcoxon signed rank test according to normality test).
- In addition, the difference in the change values for the initial, 6 months, and 1 year after simple X-ray imaging and clinical evaluation is statistically compared.
- Repeatedly measured values are verified with a linear mixed model or Generalized estimating equation (GEE) between the experimental group and the control group.
- If the P-values are  $< 0.05$ , it is judged to be a significant level.
- All data, including those included in statistical processing (ITT) through safety and efficacy evaluation, will be analyzed for those who are dropped out unless there is a valid reason or justification.
- In the case of missing values in the FAS group, it is difficult to satisfy the assumption of Missing Completely at Random (MCAR), so it is excluded and analyzed.

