## 5.0 General statistical considering

4.8 This clinical trial uses a two-sided hypothesis for the test of difference in effectiveness. It is defined as a two-sided hypothesis, as stated in the section "Sample size calculation". ( $H_0: \mu_t = \mu_c$ ,  $H_1: \mu_t \neq \mu_c$ ).

4.9 The statistical method is to test normality using the Kolmogorov-Smirnov test, then test parametric or Wilcoxon rank-sum test (nonparametric test) depending on the normal distribution.

4.10 The number of observations, mean, standard deviation, median, minimum,

and maximum values are presented for continuous variables, and frequency and percentage are presented for categorical data.

4.11 If a missing value occurs during validity analysis or a missing value occurs due to the elimination of the subject before the clinical trial is completed, this study measures the validity evaluation only once in the early and late period, and analyzes only the observed data (observed processes) without any correction to the missing values.

4.12 However, other safety assessment and other data are analyzed using data that do not replace missing values.

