4.13 Assessment of effectiveness

Repeatedly measured values are verified with a linear mixed model or Generalized estimating equation (GEE) between the experimental group and the control group. If the P-values are  $< 0.05$ , it is judged to be a significant level.

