4.14 Definition of the Evaluation and Analysis Group

The main analysis group of this clinical trial is Full analysis set, the additional analysis is for per-protocol set, and the data on stability is analyzed for safety.

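### The missing-data rule gives its reason backwards and leaves its scope and model open, so the primary comparison is at risk of bias of uncertain direction

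*Combined protocol and SAP*

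**What the plan says.** Four places in the current documents bear on missing MI values.

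- **Protocol v13.0, section 17(1)**, on missing values in the full analysis set (FAS): "they are excluded and analyzed because it is difficult to satisfy the assumption of Missing Completely at Random (MCAR". The sentence before it keeps dropouts in an intention-to-treat analysis unless there is a valid reason not to. Section 15(5) agrees: "Dropouts are included in statistical processing through safety and efficacy evaluation", again with an exception for justified reasons.
- **SAP v13.0, section 1.7**, repeats the rule and its reason: "it is difficult to satisfy the assumption of Missing Completely at Random (MCAR), so it is excluded and analyzed".
- **SAP v13.0, section 5.0, item 4.11**, gives a second reason, that "this study measures the validity evaluation only once in the early and late period", and concludes that the study "analyzes only the observed data (observed processes) without any correction to the missing values".
- **SAP v13.0, items 4.13 and 4.14**, set the test and the analysis sets: "Repeatedly measured values are verified with a linear mixed model or Generalized estimating equation (GEE) between the experimental group and the control group", and "The main analysis group of this clinical trial is Full analysis set, the additional analysis is for per-protocol set".

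On the timing of the primary measure, the hip dislocation test in Protocol v13.0 says "Measured at initial, 6 months, and 12 months". The study schedule in section 19 has matching visits at 180 and 360 days.

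The current text states no MAR assumption, no imputation and no sensitivity analysis for missing data.

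**The concern.** An unadjusted analysis of complete cases is the approach that generally relies on MCAR. The plan says MCAR is hard to satisfy and gives that as its ground for excluding, so its own reason argues against its own rule.

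The second reason fails on the documents' facts. With films at 6 and 12 months, a child who misses the last film may still have a 6-month value, and that value says something about where the hip was heading.

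Missingness may well follow the outcome. Section 15(4) of the protocol lists concurrent surgery, drug or device use that could affect the results as a reason for a subject to leave the trial, and the outcome is hip displacement. At stake is the estimate of the primary between-group difference. If *excluded* means the whole child, the main analysis set also moves towards a set of completers, against the statement that dropouts are included.

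**Working it through.** **1. The plan's design figure.** Inputs from Protocol v13.0 section 10, item 4): control progression 7.83 per year, brace 1.566, SD 8.73 in both arms, two-sided 5%, power 80%, dropout 5%.

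- Difference: 7.83 − 1.566 = 6.264.
- Normal approximation: n = 2 × (1.96 + 0.842)² × (8.73 / 6.264)² = 30.5, so 31 per arm.
- Exact t-test power: 0.794 at 31 per arm and 0.807 at 32, so 32 per arm, as planned.
- Dropout: 64 / 0.95 = 67.4, so 68 in total, as planned.

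**2. When exclusion biases the difference.** If a fraction d of an arm is missing, the observed mean is off by d × (mean of observed − mean of missing). The two arms' errors cancel if they are equal. At d = 5%, a gap of one SD in one arm only gives 0.05 × 8.73 = 0.44 points (7.0% of 6.264). A gap of one SD in opposite directions in the two arms gives 0.87 (13.9%). The sign depends on which arm loses its faster progressors: loss in the control arm shrinks the brace effect, and loss in the brace arm enlarges it.

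**3. An illustration with one dropout rule for both arms.** These assumptions are not in the documents:

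- mean 6-month change is half the annual mean (3.915 control, 0.783 brace), with SD 6.2;
- the correlation ρ between 6- and 12-month change is 0.6 to 0.8;
- a fraction f (50% or 80%) of children whose 6-month change exceeds T (8 or 10 points) has no 12-month film.

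With z = (T − 6-month mean) / 6.2, the loss is L = f × (1 − Φ(z)). The mean 12-month change among retained children is too low by B = ρ × 8.73 × f × φ(z) / (1 − L).

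Example with T = 8, f = 0.8, ρ = 0.8:

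- Control: z = 0.659, L = 0.8 × 0.255 = 0.204, B = 0.8 × 8.73 × 0.8 × 0.321 / 0.796 = 2.25.
- Brace: z = 1.164, L = 0.8 × 0.122 = 0.098, B = 0.8 × 8.73 × 0.8 × 0.203 / 0.902 = 1.25.
- Estimated difference: 6.26 − (2.25 − 1.25), about 5.3.

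| T | f | Loss, brace | Loss, control | Loss, overall | Estimate (ρ 0.6 to 0.8) | Shortfall |
|---|---|---|---|---|---|---|
| 10 | 50% | 3.4% | 8.2% | 5.8% | 5.9 to 5.8 | 5.5 to 7.3% |
| 10 | 80% | 5.5% | 13.1% | 9.3% | 5.7 to 5.5 | 9.6 to 12.8% |
| 8 | 50% | 6.1% | 12.7% | 9.4% | 5.9 to 5.7 | 6.4 to 8.5% |
| 8 | 80% | 9.8% | 20.4% | 15.1% | 5.5 to 5.3 | 12.0 to 15.9% |

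**4. The same data under other analyses.** Dropout here depends only on the observed 6-month value. A likelihood analysis of all visits therefore recovers 6.26. Unweighted GEE with an independence working correlation and a separate mean for each arm and visit estimates the 12-month mean by the plain average of the observed 12-month values. It gives the figures in the table even if only visits, and not children, are left out.

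**5. No brace effect.** With both arms at 7.83, B is the same in each and cancels, so the difference is 0. This mechanism dilutes a true effect and does not create a false one.

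**The case against.** A reader might infer that the primary comparison is biased as the plan stands. The documents do not support that. Both rules speak of missing values, not of children. Item 4.11 speaks of observed data. Dropouts are to be kept, and the FAS and per-protocol set are listed as separate sets, which would make little sense if the FAS also removed every incomplete child. On that reading, a linear mixed model on all observed visits is already a valid analysis under MAR. Even with children removed, the difference is biased only if missingness relates to the outcome differently in the two arms.

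This is a fair reading, and it rules out asserting bias as a fact. It does not settle the matter. The text never defines *excluded*, and it allows GEE, whose standard unweighted form generally needs the MCAR assumption that the plan itself doubts. One permitted analysis is sound under MAR and others are not.

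A reader might also infer that the trial will fall short of its 64 children and lose power. That is not shown. Recruiting 68 allows for 5% loss, and power at 32 per arm is 0.807. A fall to 0.764 takes 31 against 27 completers, that is 10 of 68 lost (14.7%), about three times the planned rate.

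**Conclusion.** The rule is wrong as written. Its stated reason points the other way, its second reason contradicts the visit schedule, and its scope and model are left open. If whole children are dropped, or unweighted GEE is chosen, the primary comparison is at risk of bias.

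The size rests on assumptions that are not in the documents. In the scenarios tried, child-level exclusion gives about 5.3 to 5.9 against a true 6.26, with losses of about 3 to 10% in the brace arm and 8 to 20% in the control arm. Where overall loss is near the planned 5%, the shortfall is about 5 to 7%, which is modest; it grows with dropout. The direction is uncertain. One shared dropout rule dilutes a true effect and leaves a null effect at zero, whereas rules that differ by arm could move the estimate either way.

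**What to change.** In Protocol v13.0 section 17(1), SAP v13.0 section 1.7 and SAP item 4.11, replace the rule with:

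> All randomised children with any post-baseline MI are analysed in a linear mixed model fitted by restricted maximum likelihood using all observed 6- and 12-month values (MAR); no child is excluded for a missing visit.

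Also:

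- remove the unweighted GEE option for the primary comparison, here and in SAP item 4.13;
- delete the once-early, once-late justification from SAP item 4.11;
- add one MNAR sensitivity analysis by multiple imputation, with a delta shift or a reference-based assumption for children without a 12-month film.

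The cost is wording in two documents and one extra analysis. No new data are needed. The change should be made before the allocation is unblinded to the analysts.

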**18. Treatment and treatment standards of study subjects after clinical trials**

After clinical trial, the subject will follow the further treatment plan of the hospital, the subject should pay the further cost of the treatment. Otherwise, in case of side effects occurred during the trials, and the causality with medical devices is confirmed the principal investigator should

offer the payment of the treatment.

In patients who drop out or had no reaction during the trial, the clinician should guide the subject to receive the appropriate treatment. The doctor should give instructions to re-visit the hospital at any time in case of unexpected delayed adverse effect.

#### 19. Study schedule

IRB approval to 2 years, among children with spastic cerebral palsy, test subjects were recruited, tested, and data were analyzed.

| Item                                                                                              | Screening | Before wearing auxiliary medical devices | 180 days             | 360 days                |
|---------------------------------------------------------------------------------------------------|-----------|------------------------------------------|----------------------|-------------------------|
|                                                                                                   |           | Visit 1                                  | Visit 6              | end visit               |
| Visit Window                                                                                      | 1 week    | -                                        | within $\pm 4$ weeks | $\pm 4$ weeks
Within |
| written consent                                                                                   | O         | X                                        | X                    | X                       |
| Selection/Exclusion Criteria                                                                      | O         | X                                        | X                    | X                       |
| body measurements                                                                                 | O         | X                                        | X                    | X                       |
| medical history                                                                                   | O         | X                                        | X                    | X                       |
| Frequency and type of rehabilitation treatment                                                    | O         | X                                        | X                    | X                       |
| clinical examination                                                                              | X         | O                                        | O                    | O                       |
| X-ray ( Whole spine AP, Total Hip AP , Femur AP/Lat ) hip migration index and Cobbs angle , Femur |           |                                          |                      |                         |

|                     |                                                       |   |   |   |   |
|---------------------|-------------------------------------------------------|---|---|---|---|
| in
at
io
n | anteversion
measure )                              |   |   |   |   |
|                     | Hip, knee
ROM                                      | X | O | O | O |
|                     | Satisfaction
(Likert scale)                        | X | X | O | O |
|                     | CPCHILD Poll                                          | X | O | O | O |
|                     | Adverse
reaction
inspection                     | X | O | O | O |
|                     | Pain Index
(VAS)                                   | X | O | O | O |
|                     | Medical device
manufacturing (size
measurement) | O | X | X | X |
|                     | Start wearing
medical devices                      |   | O | O | O |

If there is an X-ray result within 1 month, the existing data is used for the study.

### 2) Monitoring data and safety information

Review of key efficacy endpoints for decision to continue, change, or discontinue the study

- ① No interim analysis of effectiveness
- ② The safety review is carried out as follows, and the decision to change or discontinue is made.

I. When a serious and unexpected adverse event occurs

- (A) Decision to change or discontinue the study after review by the principal investigator
- (B) In case of notification of change or suspension of research as a result of the report by the Bioethics Review Committee

II. Safety review once every 6 months

- (A) The lead investigator decides to change or discontinue the study after reviewing all adverse reactions that occurred once every 6 months reported to the Bioethics Review Committee of each institution

III. Safety items: pain and discomfort before and after wearing the orthosis, skin change

③ **Data and safety Monitoring method and frequency: quarterly (6 months)**

④ **Reporting of adverse drug reactions, non-compliance with research, and reporting of unexpected problems**

[name] is designated and managed as the monitoring manager, and the principle investigator and working person in charge conduct monitoring every 6 months. In case of a serious adverse reaction occurring during the course of the study, report it immediately to the IRB.

- (1) Medical device adverse reaction report (fatal/life-threatening): Death or life-threatening cases within 7 days (initial report) [ based on working days]
- (2) Medical device adverse reaction report (not fatal/life-threatening): other than hospitalization or extension of hospitalization period; resulting in persistent or significant disability or dysfunction; cause congenital anomalies or abnormalities; important medical events, Etc.) Case within 15 days [ based on working days]
- (3) Report safety-related information: Collect and report at least once every 6 months
- (4) Report unexpected problems: within 15 working days
- (5) Report material non-compliance: within 15 working days
- (6) Reporting of Non-Significant Non-compliance: At least once a year

⑤ **Criteria for study discontinuation**

- (1) If the number of investigators cannot be recruited within the IRB approval period, it is decided whether to suspend or alter the study.

- (2) When the study is discontinued, the study subjects follow the treatment procedures of the hospital in relation to treatment.

